**Young Person**					
*Weight (% mBMI)*	X	X	X	X	X
*Eating Disorder Examination (EDE)*	X		X	X	X
*Eating Disorder Examination – Questionnaire (EDE-Q)*	X		X	X	X
*Clinical Impact Assessment (CIA)*	X		X	X	X
*Compulsive Exercise Test (CET)*	X			X	X
*Family Assessment Device (FAD)*	X		X	X	X
*Revised Children’s Anxiety and Depression Scale (RCADS)*	X		X	X	X
*Rosenberg Self Esteem Scale*	X		X	X	X
*EQ-5D-5L* or *EQ-5D-Y*	X		X	X	X
*Ongoing treatment post T3*					X
*Evaluation of treatment*				X	
**Parents/Guardians**					
*Family Assessment Device (FAD)*	X		X	X	X
*Parents* Versus *Anorexia Scale (PVA)*	X	2, 4, 6	X	X	
*Parent Eating Disorder Examination (PEDE)*	X		X	X	X
*Parent Eating Disorder Examination – Questionnaire (PEDE-Q)*	X		X	X	X
*Revised Children’s Anxiety and Depression Scale (RCADS) - Parent*	X		X	X	X
*EQ-5D-5L*	X		X	X	X
*Evaluation of treatment*				X	
**Siblings/Other Family Members**					
*Family Assessment Device (FAD)*	X		X	X	X
*Evaluation of treatment*				X	
*EQ-5D-5L* or *EQ-5D-Y*	X		X	X	X
**Therapist**					
*Session attendance*		X			
*Evaluation of treatment acceptability and feasibility*				X	
**Additional Health Economic Assessments**					
Healthcare resources used by young people with AN (completing a purpose-built cost questionnaire)	X		X	X	X
Non-healthcare costs incurred by young people with AN and their parents/siblings	X		X	X	X
Resources used for implementation of the FBT telemedicine intervention				X	

*%mBMI* percent median Body Mass Index, *HE* health economics

### Demographics, treatment and illness history

Demographic information will be collected to describe the young person (e.g., age, gender) and the family (e.g., socioeconomic status, employment status). The history of treatment (e.g., previous treatment and hospital admissions) and illness (e.g., duration of illness) will also be collected.

### Young person

*Percent Median Body Mass Index (%mBMI):* Weight and height will be collected on the family’s calibrated digital scales. Weight will be measured in kilograms before every treatment session, while height will be collected at T1, T2, T3 and T4. As this study is taking place via telemedicine, the weight will be taken in the young person’s home by the parents/guardians [14]. Percent median body mass index (%mBMI) will be calculated using the Centres for Disease Control (CDC) [46] charts for height, weight, gender, and age. Full symptom remission in this study greater than 85%mBMI, and an Eating Disorder Examination (EDE) score [47] within two standard deviations of population means [22].

*Eating Disorder Examination* (EDE [48];) is a standardised interview that measures the severity of eating disorder symptomology. It is a measure of present state, and, assesses both the frequency of key behaviours (including various forms of overeating and purging) and the severity of psychopathology along certain dimensions (dietary restraint, concern about eating, concern about shape, and concern about weight).

*Eating Disorder Examination – Self-Report Questionnaire* (EDE-Q [49];) is a self-report measure that was adapted from the EDE [47]. The EDE-Q is a measure of present state and, except for the items that pertain to diagnosis, it is exclusively concerned with the preceding 4 weeks. The EDE-Q assesses both the frequency of key behaviours and the severity of psychopathology along certain dimensions (dietary restraint, concern about eating, concern about shape, and concern about weight).

The *Clinical Impairment Assessment Questionnaire* (CIA [50];) is a 16-item self-report measure that measured the young person’s psychosocial impairment associated with eating disorder symptoms. The results of the CIA are particularly useful when used in conjunction with an eating disorder specific measure covering the same 28-day timeframe, like the EDE-Q.

The *Compulsive Exercise Test* (CET [51];) assesses five core features of compulsive exercise: avoidance and rule-driven behaviour, weight control exercise, mood improvement, lack of exercise enjoyment and exercise rigidity. The CET is included as excessive exercise is a common feature of an eating disorder.

The *Family Assessment Device* (FAD [52];) is a 60-item self-report measure that explores family functioning in seven subscales: problem-solving, communication, roles, affective responsiveness, affective involvement, behaviour control, and general functioning. There is evidence of a relationship between family functioning, communication, and problem-solving subscales and remission at the end of FBT [53].

The *Revised Children’s Anxiety and Depression Scale* (RCADS [54];) is a 47-item self-report questionnaire with six subscales: separation anxiety disorder, social phobia, generalised anxiety disorder, panic disorder, obsessive-compulsive disorder, and major depressive disorder plus a total internalising scale. The RCADS has been used in studies of young people with eating disorders [15] as a screener for comorbidities.

The *Children’s Global Assessment Scale* (CGAS [55, 56]) is a rating of functioning for children and young people aged 6–17 years old. The young person is given a single score between 1 and 100, based on a range of aspects related to psychological and social functioning. The score ranges from ‘extremely impaired’ to ‘doing very well’.

The *Rosenberg Self-Esteem Scale* (RSES [57];) is a 10-item self-report measure of an individual’s overall self-esteem. Low self-esteem is often observed in young persons with AN [58].

The *EQ-5D-Y* [59] or the *EQ-5D-5L* [60] (depending on the young person’s age) will be used to evaluate health and quality of life. The *EQ-5D-Y* is validated for young people up to the age of 15 years. For those older than 15 years, the EQ-5D-5L will be used.

The young person’s *Evaluation of treatment* will be completed via an online survey and semi-structured interview [14]. The semi-structured interview will explore the young person’s experience of FBT [61], barriers and challenges when receiving treatment via telemedicine and suggestions and considerations for future implementation.

### Parent/Guardian

Given the crucial role of parents/guardians in the success of FBT, a parent/guardian rating of the young person’s eating disorder symptomology and mental health status will be obtained.

*Parent Version Eating Disorder Examination* (PEDE [62],) is an interview-based version of the EDE for parents/carers [48]. The PEDE asks for parental perspective in the recent history of their child’s eating concerns, with questions formatted similarly to the EDE. It assesses both the frequency of key behaviours (including various forms of overeating and purging) and the severity of psychopathology along certain dimensions (dietary restraint, concern about eating, concern about shape, and concern about weight).

The *Parent Version of the Eating Disorder Examination Questionnaire* (PEDE-Q) [62], is a self-report questionnaire that will be used to obtain the parents’ rating of their child’s symptoms. The PEDE-Q has four subscales: restraint, eating concern, shape concern and weight concern.

The *Family Assessment Device* (FAD [52];) is a 60 item self-report measure that explores family functioning in seven subscales: problem-solving, communication, roles, affective responsiveness, affective involvement, behaviour control, and general functioning.

The *Parent* Versus *Anorexia Scale* (PVA) [63] is a seven item measure of self-efficacy of parents/guardians participating in FBT. It assesses the parent/guardians’ belief in their ability to facilitate recovery in their child and is commonly used in eating disorder research [15, 64].

The *Revised Children’s Anxiety and Depression Scale – Parent Version* (RCADS-P) [54] is a modified version of the RCADS, also with 47-items and six subscales.

The *EQ-5D-5L* [60] will be used to assess the general health and quality of life of the parent/guardians.

*Parent/Guardian evaluation of treatment* will be assessed using a short online survey and semi-structured interview to gather information from the parents regarding their opinions of the intervention and mode of delivery and will be used to determine what aspects of the treatment and telemedicine were most helpful and least helpful [14]. The semi-structured interview will explore the parent/guardian’s experience of using telemedicine to receive FBT, what they liked and did not like, barriers and challenges, perceived advantages, and suggestions and considerations for future implementation. Further, the interview will explore what factors (themes) contribute to the effectiveness of FBT and the richness of the family therapy experience, both of which can be difficult to capture in purely quantitative measures.

### Siblings/other family members

The *Family Assessment Device* (FAD [52];) is a 60-item self-report measure that explores family functioning in seven subscales: problem-solving, communication, roles, affective responsiveness, affective involvement, behaviour control, and general functioning.

*Sibling/Other family members evaluation of treatment* will be assessed using a short online survey to gather information regarding their experience of telemedicine were most helpful and least helpful as designed by the researchers for this study [14].

Depending on the sibling/other family member’s age, the *EQ-5D-5L* [60] (over 15 years) or *EQ-5D-Y* [59] (under 15 years) will be used to measure the general health and quality of life.

### Therapist

The therapist will note *Session attendance* of family members every session.

The *Therapist evaluation of feasibility and acceptability* will be measured using a brief online questionnaire and a semi-structured interview after treatment delivery for each family to explore the therapist’s experience of being in the study and delivering FBT via a telemedicine modality. In particular, the semi-structured interview will explore the therapist’s experience of utilising telemedicine to deliver FBT, what components of the alternate mode of delivery enhanced their clinical practice, what were the barriers and challenges, and suggestions and considerations for future implementation.

### Health economics

The participants’ health-related quality of life will be collected using the EQ-5D measures noted above. Resource use collected through the costs and consequences analysis will focus on those healthcare resources associated with the FBT telemedicine intervention or standard care (face-to-face), including the cost of training staff, time costs of health professionals seen by participants for this treatment (therapists and coordinators), laboratory costs, hospitalisations, GP visits, specialist visits, allied health other than through the study, and prescribed treatments and medications (i.e. a micro-costing approach). This resource use data will be collected using purpose-built cost questionnaires administered at T1, T2, T3 and T4. Unit costs will be obtained from a combination of market process (e.g. hourly wage rate), published data and estimates provided by individuals (especially for out-of-pocket costs).

### Primary outcomes

To determine treatment effectiveness (Aim 1), an increase in %mBMI to greater than 85% will be used as an indicator of remission from pre-treatment (T1) to post-treatment (T3) and pre-treatment (T1) to six-month follow-up (T4). In addition, changes from T1 to T3 and T1 to T4 in eating disorder symptomology (global score on the EDE/EDE-Q and PEDE/PEDE-Q), exercise behaviours (CET) and impairment (CIA); general mental health (RCADS and RCADS-P); quality of life (EQ-5D-5L and EQ-5D-5L-Y); family functioning (FAD); and, parental self-efficacy (PVA).

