## Background

Anorexia nervosa (AN) is a serious psychiatric disorder, with numerous negative physical and psychological health impacts [1–3]. It is the third most common chronic disorder affecting adolescent girls [4], although AN affects both genders and is present across the entire lifespan [5]. Children and adolescents are especially vulnerable to the physical consequences of AN such as stunted growth, poor bone health, cardiac complications, infertility, and changes to brain structure [6]. The average duration of AN is 5 to 7 years [7], although long-term follow-up evidence suggests that after a 10-year duration of illness, only 30% of individuals are recovered [8]. Individuals diagnosed with AN have approximately 12 times greater risk of death, and a 57 times greater risk of suicide compared to same-age peers [2]. Given the seriousness of the disorder, treatment must be delivered efficiently and effectively.

Currently, Family-Based Treatment (FBT) is the most efficacious therapy for adolescents with AN [9–11] recommended by international clinical practice guidelines [12, 13]. FBT has been manualised as a face-to-face outpatient behavioural intervention and emphasises parental support as the primary resource in the recovery of adolescents with AN [14]. Several randomised controlled trials (RCTs) have demonstrated the efficacy of FBT for adolescent AN [10, 15–20]. Remission rates are particularly promising for adolescents with short illness duration [11, 16, 21]. The average remission rate for all participants at the end of FBT is approximately 40% [11, 22, 23]. An average of 75% of young people demonstrate improvement in weight and eating-related symptomatology at end of FBT [16].

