### Participants

Young people, aged between 12 and 18 years who meet diagnostic criteria for AN as defined by the fifth edition of the *Diagnostic and Statistical Manual of Mental Disorders (DSM-5)* [41] will be recruited for this study. Given the importance of involving the whole family in treatment, the parents/guardians responsible for the young person’s recovery as well as siblings and any other family members involved in treatment will also be recruited. Participants will be a resident of a regional or rural health district in NSW, Australia. The reason for selecting regional and rural health districts is due to the already great need for specialist care in these regions given eating disorder services are sparse in usual service delivery circumstances. Primarily, participants will be recruited via the already existing referral pathways for mental health service for young people, such as via medical practitioners, schools, and local mental health services.

Three therapists from each of the five regional and rural health districts eligible for the study have been recruited (*n* = 15). Each therapist has the capacity to work with *n* = 2 families each year, with a maximum of *n* = 4 families during the study. The therapists providing treatment will contribute to the evaluation, and thus will be enrolled as participants. All therapists had to meet a minimum level of training and experience in FBT, obtain management support to enrol in the study, and commit to participate in additional training and regular supervision.

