### Inclusion/exclusion criteria

The young person with AN must be medically stable for outpatient treatment verified by their medical professional [42]. The family must be committed to engaging in FBT, not be engaged in any other psychological or dietetic treatment for AN, have access to a computer or tablet device with videoconferencing functions, a reliable internet connection, access to a telephone or mobile phone if internet unavailable, and access to a reliable digital weighing scale at home. The study can provide some of these requirements to families to ensure equity of inclusion. Young people who require inpatient treatment for a physical or psychiatric illness, are dependent on alcohol or other substances, have acute suicidality, currently pregnant, or under compulsory treatment orders, are excluded from participating in this study.

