### Data analysis

#### Aim 1: Effectiveness of delivering FBT via telemedicine

A mixed model logistic regression will be used to evaluate the effectiveness of FBT delivered via telemedicine, using change of %mBMI as the primary outcome from T1 to T3 and from T1 to T4. To determine the effectiveness, secondary analyses, again using a mixed model regression, will compare the young persons’ global EDE and EDE-Q, as well as the parents/guardians PEDE and PEDE-Q scores. Further, the young persons’ responses on the CIA, CET at T1, T2, T3 and T4 will be compared. The young persons’, parent/guardians, and sibling/other family members responses on the FAD and EQ-5D-5L/EQ-5D-Y in addition to the parent/guardian responses on the PVA will be analysed to determine changes in family functioning, parental efficacy, and wellbeing from T1 to T3 and T1 to T4.

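### The primary endpoint is stated in three non-equivalent ways, the study's own remission definition is never assigned to an analysis, and participants above 85% mBMI at T1 have no defined classification

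*Protocol article*

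**What the plan says.** Three places in the protocol article describe the effectiveness endpoint.

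- **Young person (measures), %mBMI paragraph:** "Full symptom remission in this study greater than 85%mBMI, and an Eating Disorder Examination (EDE) score [47] within two standard deviations of population means". This is a status with two components, and no change from baseline is required.
- **Primary outcomes:** "an increase in %mBMI to greater than 85% will be used as an indicator of remission", from T1 to T3 and from T1 to T4. This is weight alone, and it is worded as an increase. Change in global EDE/EDE-Q then follows as one of several further outcomes under the same heading.
- **Data analysis, Aim 1:** a mixed model logistic regression "using change of %mBMI as the primary outcome from T1 to T3 and from T1 to T4". EDE comes afterwards: "secondary analyses, again using a mixed model regression, will compare the young persons’ global EDE and EDE-Q".

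On entry, the Participants section recruits "Young people, aged between 12 and 18 years who meet diagnostic criteria for AN" by DSM-5, and the Inclusion/exclusion criteria add that "The young person with AN must be medically stable for outpatient treatment verified by their medical professional". Neither section attaches a %mBMI figure to entry. Overall study design gives a total of 40 families and describes a pre- and post-implementation study. Table 1 schedules both %mBMI and the EDE at T1, T2, T3 and T4.

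**The concern.** A remission rate needs one rule. Here the definition given for this study is a composite, the primary outcome uses only its weight component, and the analysis section names a continuous quantity but fits a model for a binary one. The analyst has to choose the binary variable: the composite, weight status above 85% at each visit, or crossing from at or below 85% to above it.

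The choice has consequences because entry is not tied to a %mBMI limit. A participant above 85% at T1 cannot cross the threshold, so crossing coding makes that person a certain non-success. Status coding makes the same person a success at T3 or T4 simply by remaining above. The text does not say which applies, or whether such participants are in the denominator.

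All recruited families receive telemedicine FBT, with no randomised control group, so the reported T3 and T4 remission rates carry much of the message on effectiveness. If the rule is chosen after the data are seen, the rate can be moved by definition alone.

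**Working it through.** The document states no figure for this endpoint, so there is nothing to reproduce. The check is a comparison of definitions, followed by an illustration of how far they can diverge.

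**Step 1. The three statements side by side**

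| Place | Variable | Type | EDE part of it? | Change needed? |
|---|---|---|---|---|
| Young person (measures) | >85% mBMI and EDE within the limit | binary status | yes | no |
| Primary outcomes | rise in %mBMI to >85% | binary, worded as a crossing | no, listed separately | yes |
| Data analysis, Aim 1 | change of %mBMI in a logistic model | continuous variable, binary model | no, secondary | yes |

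No sentence links the rows. The first row, the only one called remission in this study, appears in neither the outcome list nor the analysis.

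**Step 2. Weight status against the composite**

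Let w be the share above 85% mBMI at T3 and e the share of those who also meet the EDE limit. Then composite = w × e, which can never exceed w. With w = 60% (assumed):

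- e = 50%: 0.60 × 0.50 = 30%
- e = 70%: 0.60 × 0.70 = 42%
- e = 90%: 0.60 × 0.90 = 54%

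**Step 3. Status against crossing**

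Inputs: N = 40 (Overall study design); f = share already above 85% at T1 (not in the document; assumed 10% to 50%); r = share of the remainder who cross (assumed). Those already above are taken to stay above.

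- Status, all enrolled: f + (1 − f) × r
- Crossing, all enrolled: (1 − f) × r
- Crossing among those at or below 85% at T1: r

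| f | Number above at T1 | Status, r = 0 | Status, r = 40% | Crossing over all 40, r = 40% | Crossing among those at or below 85%, r = 40% |
|---|---|---|---|---|---|
| 10% | 4 | 10% | 46% | 36% | 40% |
| 20% | 8 | 20% | 52% | 32% | 40% |
| 30% | 12 | 30% | 58% | 28% | 40% |
| 50% | 20 | 50% | 70% | 20% | 40% |

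Only the last column does not depend on how many participants start above the threshold.

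**Step 4. Direction of the difference between composite and crossing**

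Take r = 40% and e = 70%, with e applied to everyone above 85%.

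- f = 0: crossing = 40%; composite = 0.40 × 0.70 = 28%. The composite is lower.
- f = 30%: crossing = 0.70 × 0.40 = 28%; composite = 0.58 × 0.70 = 41%. The composite is higher.

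Moving to the composite can therefore raise or lower the rate relative to the literal wording of the primary outcome.

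**The case against.** Four points can be made for the plan.

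1. **The labels differ.** One section speaks of full symptom remission and the other of an indicator of remission, with EDE change reported under the same heading. This can be read as two tiers. It softens the conflict, but no text says that there are two tiers or which rate is the headline, and the full definition still reaches no analysis.

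2. **Coding and denominators are usually left to the full protocol or SAP.** That is true of detail. Here, however, the article itself states the endpoint in three ways, and a later SAP would have to depart from at least one of them.

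3. **The number affected may be small or zero.** The article gives no baseline %mBMI distribution, and everyone must meet DSM-5 criteria for AN. This stands: the share above 85% at T1 cannot be derived, and every f used above is an assumption.

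4. **A repeated-status model with a time effect uses T1 status.** This also stands. The exposure is mainly in the rates reported at T3 and T4.

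A reader might infer that participants already above 85% will be counted as remitted without any change. The documents do not support that as stated. The primary outcome asks for an increase, so an unchanged participant does not meet it as written; the result follows only from status coding. A reader might also set the rate beside the Background statement that "The average remission rate for all participants at the end of FBT is approximately 40" per cent. The article does not define remission for that figure and plans no test against it, so no conclusion about that comparison is drawn here.

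**Conclusion.** The point holds as a conflict between stated rules for the primary endpoint. The protocol gives a weight-plus-EDE status, a weight-only increase, and a continuous change placed in a logistic model. These are not interchangeable, and the composite that the protocol calls remission in this study is never analysed. Because no numeric %mBMI limit is set at entry, the classification of anyone above 85% at T1 is open: such a person can never succeed under crossing coding, and under status coding succeeds by staying above the threshold.

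The size cannot be fixed from the document. In the illustration with f = 30%, r = 40% and e = 70%, the same 40 participants give 28%, 41% or 58% depending on the rule. Those figures show sensitivity to the definition and do not predict the trial's result. If nobody is above 85% at T1, the open classification has no effect, but the difference between weight alone and weight plus EDE remains.

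**What to change.** Align the Young person (measures), Primary outcomes and Aim 1 analysis sections on one remission endpoint.

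- **Remission:** use the composite from the measures section, at T3 and T4, as the binary outcome of the mixed logistic model. Report T1 status on the same definition and include T1 as the baseline time point. This is needed because the composite is itself a status measure, and anyone meeting it at T1 should be visible.
- **Weight threshold:** label it as a separate weight indicator, distinct from remission, and report it among participants at or below 85% mBMI at T1.
- **%mBMI change:** analyse it as a continuous outcome with a linear mixed model.

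The cost is small. Both %mBMI and the EDE are already scheduled at T1 to T4, so no new data are needed. The weight indicator will have a smaller denominator (28 instead of 40 if 30% start above the threshold). The reported remission rate may move in either direction. If few or no participants meet the composite at T1, the T1-to-T3 odds ratio may be unstable or not estimable, so the proportions at T3 and T4 should be reported with confidence intervals alongside the model.

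### The protocol gives two conflicting lists of primary outcomes for Aim 1, and %mBMI itself appears in two forms at two unranked time points

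*Protocol article*

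**What the plan says.** The section Primary outcomes ties its list to Aim 1. It opens with "an increase in %mBMI to greater than 85% will be used as an indicator of remission from pre-treatment (T1) to post-treatment (T3", and names the six-month follow-up (T4) in the same way. It then continues: "In addition, changes from T1 to T3 and T1 to T4 in eating disorder symptomology (global score on the EDE/EDE-Q and PEDE/PEDE-Q". Exercise behaviour (CET) and impairment (CIA) follow, and the list closes with "general mental health (RCADS and RCADS-P); quality of life (EQ-5D-5L and EQ-5D-5L-Y); family functioning (FAD); and, parental self-efficacy (PVA". The section Secondary outcomes covers Aims 2 and 3 and lists none of these instruments as an effectiveness outcome.

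The section Data analysis, Aim 1, specifies a mixed model logistic regression "using change of %mBMI as the primary outcome from T1 to T3 and from T1 to T4". The next sentence reads "To determine the effectiveness, secondary analyses, again using a mixed model regression, will compare the young persons’ global EDE and EDE-Q", and goes on to the parents' PEDE and PEDE-Q. CIA and CET come after that. "The young persons’, parent/guardians, and sibling/other family members responses on the FAD and EQ-5D-5L/EQ-5D-Y" are then to be analysed together with the PVA. None of these last five instruments is called primary or secondary.

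**The concern.** The outcome section and the analysis section should agree on what is primary, because that decides which result answers Aim 1. Here the same four eating disorder measures are primary in one place and secondary in another. Seven more instruments are primary in the first section and then either unranked or absent in the second. An analysis plan written later cannot follow both sections.

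%mBMI is the one outcome that both sections treat as primary, but it is not a single quantity. It is a threshold in one section and a change in the other, over two intervals with no order between them. If the threshold result and the change result differ, or T3 and T4 differ, the protocol does not say which one decides. That leaves room to select the deciding result after the data are seen.

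**Working it through.** The protocol states no significance level, power or number of tests, so there is no error-rate figure of its own to reproduce. The check is a comparison of the two sections, followed by an illustrative calculation.

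**Side by side**

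| Outcome | Primary outcomes section | Aim 1 analysis section |
|---|---|---|
| %mBMI | Primary, as reaching more than 85%; T1–T3 and T1–T4 | Primary, as change, in a logistic model; T1–T3 and T1–T4 |
| EDE, EDE-Q, PEDE, PEDE-Q | Primary | Secondary |
| CIA, CET, FAD, EQ-5D, PVA | Primary | Analysed, no rank |
| RCADS, RCADS-P | Primary | Not mentioned |

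Two details add to the conflict. The analysis section says that its secondary analyses also serve to determine effectiveness. The Measures section (Young person) gives a further definition, full symptom remission, which combines more than 85% mBMI with an EDE score within two standard deviations of population means.

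**Count of contrasts in the Primary outcomes section**

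- Instruments, with the two EQ-5D versions counted as one: %mBMI + 4 (EDE, EDE-Q, PEDE, PEDE-Q) + 7 (CET, CIA, RCADS, RCADS-P, EQ-5D, FAD, PVA) = 12.
- Two intervals each: 12 × 2 = 24.
- Table 1 schedules no PVA at T4, so the T1–T4 contrast for PVA cannot be computed: 24 − 1 = 23.
- The analysis section takes FAD and EQ-5D from three respondent groups. Counting these separately adds 2 × 2 = 4 outcomes: 16 × 2 − 1 = 31.

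**Illustrative chance of at least one false positive**

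Assumptions, none from the protocol: two-sided 5% level for each test, and no true change on any outcome. For k independent tests the chance is 1 − 0.95^k.

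- k = 2 (%mBMI only, both intervals): 1 − 0.95² = 0.0975, or 9.8%.
- k = 23: 1 − 0.95²³ = 0.693, or 69%.
- k = 31: 1 − 0.95³¹ = 0.796, or 80%.

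The instruments overlap, so independence gives the high end. Simulation of equally correlated two-sided z tests (200,000 replicates) gives:

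| Correlation | k = 2 | k = 23 |
|---|---|---|
| 0.3 | 9.5% | 58% |
| 0.5 | 9.0% | 45% |
| 0.7 | 8.4% | 31% |
| 0.9 | 7.0% | 16% |

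One outcome in one form at one time point would be tested at the assumed 5%.

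**The case against.** A fair opponent would say that the intent is clear enough. %mBMI comes first in one section and is the only outcome called primary in the other, so the questionnaires are supporting measures under a loose heading. That is a plausible reading. It does not explain why the Secondary outcomes section leaves every Aim 1 instrument out, and it does not settle the form or the time point of %mBMI.

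A reader might infer that the protocol allows effectiveness to be declared on whichever of two dozen tests turns out significant. It does not say so: there is no success rule of that kind, and no significance level. The gap is that no rule says which result decides. A reader might also object that no error control is described. Multiplicity handling is commonly left to the analysis plan, which is not shown here, so its absence is not part of this point.

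The opponent is also right about the percentages. They need an assumed 5% level, and the larger ones lean on independence, although EDE and EDE-Q are interview and questionnaire forms of one construct and several parent measures mirror those of the young person. They further assume no change at all over a 9-month treatment. The Background reports that on average 75% of young people improve by the end of FBT, so that null is implausible in a single-group pre-post study. The percentages show how much selection the text could allow; they do not predict this trial's error rate.

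**Conclusion.** The point holds as a contradiction in the current text. The two sections disagree on the rank of eleven instruments: four are primary in one and secondary in the other, five are primary and then unranked, and two are primary and then missing from the Aim 1 analysis. The shared primary, %mBMI, has two forms and two unranked intervals. An unseen analysis plan does not cure this, because the protocol itself states what is primary and does so in two ways.

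Under the assumptions above, the illustrative size runs from 9.8% (two %mBMI intervals) to 69% (23 collectable contrasts), both lower with correlation. A reader might take the 69%, or the 80% with respondents split, as the trial's false-positive rate; the documents do not support that. Because the analysis section already points to %mBMI, this is a should-fix matter of reconciliation. It does not invalidate the design.

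**What to change.** Amend both sections so that they name the same single primary outcome, based on %mBMI. Choose one form and match the model to it: a binary indicator of more than 85% with a logistic model, or continuous change with a linear mixed model. Choose one time point, for example T3 (end of treatment). The documents do not dictate these choices; what matters is that both sections make the same one. Changing only the Primary outcomes section would leave both intervals primary in the analysis section.

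Label the other interval and all other instruments as secondary, and add RCADS and RCADS-P to the Aim 1 analysis. Report the secondary outcomes as estimates with 95% confidence intervals, and state that none of them alone will be used to declare effectiveness. Drop the T1–T4 contrast for PVA or add the assessment to Table 1.

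The cost is a dated protocol amendment with a reason given, since the study began in April 2020, and fewer outcomes that can support a confirmatory claim. Apart from any added PVA assessment, no data collection changes.
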